### Interim analyses {21b}

Not applicable.

### Methods for additional analyses (e.g. subgroup analyses) {20b}

Not applicable.

### Methods in analysis to handle protocol non-adherence and any statistical methods to handle missing data {20c}

Not applicable.

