### Strategies to improve adherence to interventions {11c}

This study is based on the network platform for follow-up by a variety of means to improve patient adherence. The doctor in charge of the patients will prescribe prescription and instruct them how to use the drug by Wechat Mini Programs. The research assistant of each research center will invite the patients to the Wechat group, remind them of the medication time, make an appointment for follow-up, and solve any questions raised by the patients in the Wechat group in time. Medication compliance will be calculated as the actual taken amount of study medication documented in a participant’s daily diary divided by the total amount planned for the participant.

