### Sample size {14}

The sample size calculation was conducted using the PASS software version 25 (NCSS, LLC. Kaysville, Utah, USA). Previous studies have shown that one-year recurrence rate of stroke patients in China was 17.7% [1]. The underlying assumption was a decline of the recurrence rate of stroke from 17.7% to 14.7%. The sample size of the experimental group and the control group was about 3168 with at least 90% power and an overall two-sided alpha level of 0.05. Taking approximate dropouts of 15% into account, the number of participants recruited was estimated to be 3727 each group. Therefore, 8000 patients will be recruited for this trial.

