#### Unblinding and allocation

At the end of the study cycle, the researchers will reveal the actual medication information of the patients, taking patients with good butylphthalide compliance as the butylphthalide group, and patients without taking butylphthalide and patients with poor compliance as the control group, and compare the difference of outcomes between the two groups.

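### Item {20c} calls non-adherence and missing-data methods not applicable, although 15% dropout is planned, adherence defines the groups, and the diary formula can move butylphthalide takers into control

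*Protocol article*

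**What the plan says.** All references are to the protocol article.

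- **Item {20c}.** The section headed "Methods in analysis to handle protocol non-adherence and any statistical methods to handle missing data {20c" has one reply: not applicable. It does not refer the reader to another document.
- **Sample size {14}.** "Taking approximate dropouts of 15% into account, the number of participants recruited was estimated to be 3727 each group".
- **Plans for assessment and collection of outcomes {18a}.** Centres with missing follow-up information or high dropout are to be removed from further participation, so both are expected.
- **Strategies to improve adherence {11c}.** Compliance is the amount documented in the participant's "daily diary divided by the total amount planned for the participant".
- **Explanation for the choice of comparators {6b} and the Fig. 1 legend.** Compliance of 80% to 120% is good, and anything outside that range is poor. Here the numerator is the actual number of tablets, and the diary is not mentioned.
- **Unblinding and allocation.** Groups are formed at the end of the study, "taking patients with good butylphthalide compliance as the butylphthalide group". Patients who did not take the drug and poor compliers form the control group.
- **Concealment mechanism {16b} and Data collection.** Forms sent to patients through the Mini Program are also a source of medication information.
- **Statistical methods {20a}.** Recurrence is analysed by Kaplan–Meier, log-rank and Cox; NIHSS and mRS by t-test or Wilcoxon test; propensity score matching is planned. No censoring rule and no rule for missing scores or blank diary entries is given.

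**The concern.** The reply under {20c} is a statement, and it conflicts with the rest of the protocol. Missing follow-up is budgeted for, and non-adherence determines group membership.

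The second half of the problem is more specific. Where compliance is documented intake over planned intake, an undocumented dose adds nothing to the numerator. A patient who took the capsules but kept a poor diary is then rated a poor complier and counted as a control. A gap in the records becomes a change of comparison group, and no stated rule prevents it.

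The consequence depends on why records are missing. If gaps are unrelated to outcome, the groups are mixed and the effect is diluted. If a recurrence during treatment makes a patient stop keeping the diary, the event is carried from the butylphthalide group to the control group, and a benefit can appear where none exists. Kaplan–Meier and Cox do not protect against this, because the group label itself has changed.

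**Working it through.** **1. The plan's own figures.** Inputs from Sample size {14}: 17.7% and 14.7%, two-sided alpha 0.05, power 90%.

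n per group = [1.960·√(2·0.162·0.838) + 1.282·√(0.177·0.823 + 0.147·0.853)]² / 0.03² = 3168, as stated.

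Allowing for dropout: 3168 / 0.85 = 3727.06, against 3727 stated. The sample-size arithmetic is sound and is not in dispute.

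**2. Scale of planned loss.** 15% of 8000 = 1200 patients. With equal groups of 4000 (an assumption of the calculation, since patients choose their treatment), 4000 × 0.85 = 3400 per group remain, with power 91.9%.

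**3. When the diary formula moves a patient.** The threshold is 80%, so more than 20% of planned doses must be undocumented. Over 90 days, 0.20 × 90 = 18 days. This assumes complete intake on all other days and a plan of exactly 90 days; the protocol says 90 days or more.

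**4. Misclassification unrelated to outcome.** Assume the planned effect is real, 3400 per group, and a share m of takers is moved to control. The control rate becomes (3400·0.177 + 3400·m·0.147) / (3400·(1+m)). For m = 10%: (601.8 + 49.98) / 3740 = 17.43%, a difference of 2.73 points.

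| Share moved | Group sizes | Difference (points) | Power |
|---|---|---|---|
| 0% | 3400 / 3400 | 3.00 | 91.9% |
| 5% | 3230 / 3570 | 2.86 | 89.2% |
| 10% | 3060 / 3740 | 2.73 | 86.1% |
| 20% | 2720 / 4080 | 2.50 | 78.6% |

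A random 5% is enough to use up the margin above 90%.

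**5. Misclassification that depends on recurrence.** Assume no drug effect, 17.7% in both groups and 3400 each, so 601.8 recurrences per group. A share f of takers with a recurrence is moved to control.

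For f = 10%, 60.2 patients move:
- butylphthalide: (601.8 − 60.2) / (3400 − 60.2) = 16.2%
- control: (601.8 + 60.2) / (3400 + 60.2) = 19.1%

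| f | Patients moved | Butylphthalide | Control | False benefit (points) |
|---|---|---|---|---|
| 5% | about 30 | 17.0% | 18.4% | 1.5 |
| 10% | about 60 | 16.2% | 19.1% | 2.9 |
| 20% | about 120 | 14.7% | 20.5% | 5.8 |

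At f = 10% a two-proportion test would be significant about 88% of the time. The planned effect is 3.0 points. A patient who stops documenting at recurrence falls below 80% only if that happens before day 72 of a 90-day plan (0.80 × 90), so only early recurrences can act this way. The documents do not say what share of recurrences is early.

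**6. Sensitivity to loss to follow-up.** Suppose 15% of the butylphthalide group are lost, those followed show 14.7%, and lost controls resemble followed controls (17.7%). The 3-point effect vanishes if the lost butylphthalide patients have a recurrence rate of (0.177 − 0.85·0.147) / 0.15 = 34.7%.

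**The case against.** **The reply may be an unfilled template line.** {20b} is also answered as not applicable although {20a} plans subgroup analyses, and {21b} is so answered although {25} gives the data monitoring committee interim analysis. Imputation models and detailed censoring rules are also commonly left to a full protocol or analysis plan. That stands for the detail: its absence alone is no fault. It does not remove the conflict, because the reply denies a need that other sections create, and the grouping formula is stated in this document.

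**A non-adherence rule does exist.** This stands. {6b} and the allocation section send poor compliers to control. For that half, the fault is that {20c} disagrees with the rule, not that there is none.

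**A reader might infer that dropouts are analysed as complete cases.** The protocol does not say so. Kaplan–Meier and Cox ordinarily censor dropouts and keep a recurrence recorded before contact ended. A calculation on the raw proportions among completers, with outcome-related loss in one group only, would therefore not represent the planned recurrence analysis. Standard censoring still assumes that loss is unrelated to recurrence, and it does nothing for NIHSS, mRS or blank diary days.

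**A reader might infer that the protocol declares a blank day to be a day without drug.** It does not say this. It follows from the {11c} formula only if the diary governs, and other sections name tablet numbers and patient-completed forms. What stands is that the governing source is unsettled and that one of the stated formulas has this effect.

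**A reader might infer that the bias must favour butylphthalide.** The documents give no reason why patients stop documenting, and random gaps work in the opposite direction.

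**Conclusion.** The point holds in limited form. The reply under {20c} contradicts the 15% dropout allowance, the missing follow-up foreseen in {18a}, and the adherence-based grouping. The {11c} formula, followed as written, places takers with incomplete diaries in the control group, and the protocol does not settle which medication record governs.

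On assumed shares, moving 10% of takers at random costs about 6 points of power. Moving 10% of takers with a recurrence creates a false benefit close to the whole planned effect. Neither share comes from the documents, equal group sizes are assumed, and the net direction is unknown. The documents do not support the stronger conclusions that the result is certain to favour butylphthalide or that the recurrence analysis is restricted to completers. The matter should be corrected before groups are formed at the end of the study.

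**What to change.** Replace the reply under {20c} with text that agrees with {6b}, {14}, {20a} and the allocation section:

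1. **Compliance source.** Name one source among the data already collected, and use the same definition in {6b}, {11c} and Fig. 1.
2. **Blank entries.** Treat them as missing, not as zero intake. Do not let missing records alone place a patient in the control group. For example, keep patients recorded as having started butylphthalide in that group, with a sensitivity analysis that reclassifies or excludes them.
3. **Recurrence.** State that follow-up is censored at the last contact with known status. Add a fixed sensitivity analysis that varies the recurrence risk among those lost, separately by group. Censoring weights alone would not suffice, because they cannot correct for loss driven by a recurrence that was never recorded.
4. **Scores.** Use multiple imputation for mRS from baseline and earlier scores, and for NIHSS from baseline, since NIHSS is captured after discharge only in the first month.

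The cost is wording and some extra programming. No new data are needed if the compliance source is one already collected. The estimate may turn out less favourable to butylphthalide.

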### Plans to give access to the full protocol, participant level-data and statistical code {31c}

Not applicable.

## Oversight and monitoring

### Composition of the coordinating centre and trial steering committee {5d}

The School of Medicine of Northwestern University of China is the coordination center of this study, which is responsible for the supervision and ethical review of the whole research process to ensure the proper implementation of this trial. When the trial starts, the coordination center will coordinate and monitor 78 sub-centers. The coordinating center will track trial progress at least once a month by networking, phone call, email or onsite monitoring. Every research assistent is responsible for coordinating and organizing the enrolment, informed consent, and follow-up procedures at their local sites. There are no stakeholders and public participation groups in this trial.

### Composition of the data monitoring committee, its role and reporting structure {21a}

The study will be monitored by an independent data monitoring committee (DMC). The monitor regularly conducts onsite monitoring and reviews the CRFs to ensure participants’ rights and interests, compliance with the trial protocol, source data validity, data accuracy, and data integrity.

### Adverse event reporting and harms {22}

If an adverse event occurs in a clinical trial, the committee of medical experts will determine whether it is related to basic therapeutic drugs. The organizer will provide treatment fees and corresponding economic compensation for the test-related damage in accordance with the provisions of “Drug Clinical trial quality Management Code of China”.

### Frequency and plans for auditing trial conduct {23}

An independent auditor will audit this trial, regarding trial conduct and compliance with the protocol, standard operating procedures, good clinical practice, and the applicable regulatory requirements.

### Plans for communicating important protocol amendments to relevant parties (e.g. trial participants, ethical committees) {25}

Any major amendments need to be reported to the Medical Ethics Committee of Northwestern University of China before they can be implemented. And DMC will be responsible for data monitoring, interim analysis, assessment of adverse events and review of core trial procedures and documentation, discussion of any revisions to the main study protocol, and making the final decision to terminate the trial.

## Dissemination plans {31a}

The full protocol and datasets analyses of the current study are available from the corresponding author on reasonable request. The primary investigators and sponsor will communicate the trial results to participants and all the investigators involved. The trial results will be submitted to national or international conferences or peer-reviewed journals with the sponsor’s permission.

## Discussion

A systematic review found evidence suggesting that the combination of NBP and conventional neuroprotective agents improves functional recovery at 90 days after ischemic stroke compared with conventional drugs alone [6]. And many randomized, double-blind, placebo-controlled, multicenter clinical trials also suggest that NBP may be a safe and effective treatment for ischemic stroke [7–10]. This trial will be exploring the efficacy and safety of butylphthalide in secondary prevention of ischemic stroke, in order to expand the application of butylphthalide soft capsules and provide new evidence for enriching the secondary prevention of stroke.

In addition, this trial is a real-world trial highlighting the practicability of the research results. We have a larger sample size and a longer follow-up time, which can better reduce the sampling error and more easily detect other adverse events. This research can better represent the target population, and its treatment methods are close to the actual treatment [31], which can better reflect the effectiveness of butylphthalide in the real world.

The most important feature of this study is to use the network platform to complete the follow-up. In previous studies, it is difficult for patients to complete NIHSS score or mRS score in follow-up by returning to the hospital, resulting in a large number of dropouts and incomplete information. In this study, researchers score the mRS and NIHSS of the subjects by making a video call with them. So it could eliminate the inconvenience of patients returning to hospital for follow-up. In addition, by Wechat group, Wechat Mini Programs and other ways, we could manage patients, remind patients of medication time, guide patients how to use drugs, and greatly increase patients’ compliance with medication. It is critical for the management of medical big data in the future in China. In the future, we may develop artificial intelligence, machine learning and other means to standardize scoring.

## Trial status

This trial is in the recruitment phase. Patient recruitment begins in December 2020 and is expected to be completed in June 2023.

## Data Availability

The datasets generated and analyzed during the current study are available from the corresponding author upon request.

## Abbreviations

NBP: Dl-3-n-butylphthalidle
RCT: Randomized controlled trial
NIHSS: National institutes of health stroke scale
MRS: Modified Rankin Scale
ChiCTR: Chinese Clinical Trial Registry.
SPIRIT: Standard Protocol Items
SAE: Serious adverse events
CRF: Case report form
eCRF: Electronic case report form
EDC: Electronic Data Capture System
AEs: Adverse events
DMC: Data monitoring committee
